## Pharmacokinetic Analysis

The blood concentration-time curves for each subject will be plotted for each time point. Based on the blood concentration-time data, pharmacokinetic parameters will be calculated using the standard non-compartmental model method in the WinNonlin software. The main pharmacokinetic parameters obtained will include T_max_, C_max_, AUC_0-t_, AUC_0-∞_, t_1/2_, MRT, CL, Ke, and V. Descriptive statistics will be used to list the mean, standard deviation, median, maximum, and minimum for the continuous data.

Dose proportionality analysis will be performed using single-dose pharmacokinetic parameters (PKPS) and analyzed with a power function model to examine the relationship between AUC, C_max_, and dose. The linearity criterion will be that the 95% confidence interval for the β value includes 1.

Accumulation will be assessed by comparing Cmax and AUC_SS_ from multiple dosing with C_max_ and AUC_0-48h_ from single dosing to calculate the accumulation ratio.。

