### Pharmacokinetic Study

#### Pharmacokinetics in Rodents

**（1）Pharmacokinetic Study in SD Rats**

After a single intravenous injection of Purinostat Mesylate at doses of 1, 3, and 10 mg/kg, the average initial concentrations (C0) in male and female SD rats were 736 ± 66.5, 2880 ± 566, and 11500 ± 1790 ng/mL, respectively. The plasma clearance rates (CL) were 301 ± 20.0, 205 ± 36.4, and 131 ± 12.8 mL/min/kg, respectively. The steady-state apparent volume of distribution (Vdss) was 1.43 ± 0.135, 1.13 ± 0.241, and 0.948 ± 0.125 L/kg, respectively. The half-lives (T1/2) were 3.79 ± 0.511, 4.21 ± 0.248, and 6.24 ± 1.57 min, respectively. The area under the curve (AUC_0-last_) values were 55.3 ± 3.68, 248 ± 36.1, and 1280 ± 122 ng.h/mL, respectively. After daily intravenous injections of 3 mg/kg Purinostat Mesylate for 7 consecutive days, the average AUC_0-last_ on day 7 for both male and female rats was 332 ± 43.6 ng.h/mL.

In the dose ranges of 1 to 3 mg/kg and 3 to 10 mg/kg, both C0 and AUC_0-last_ values in male and female rats increased proportionally with the dose. Across the dose range of 1 to 10 mg/kg, the C0 values increased proportionally with the dose, while the AUC_0-last_ values increased slightly more than proportionately. A tenfold increase in dose corresponded to a 21.7-fold and 24.4-fold increase in AUC_0-last_, respectively, for male and female rats.

At the doses of 1, 3, and 10 mg/kg, there were no significant gender differences in C_0_ and AUC_0-last_ values between male and female rats.

Following daily intravenous injections of 3 mg/kg for 7 consecutive days, there were no significant differences in AUC_0-last_ between days 1 and 7 for both male and female rats, indicating no abnormal accumulation.

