The starting dose will be 1.2 mg/m², and dose escalation will be conducted according to the Modified Fibonacci Scheme, with escalation increments of 100%, 67%, 50%, 40%, 33%, and 33%. Only after completing the single and multiple administration phases of the previous dose group, and based on the tolerability and pharmacokinetic results of that dose group, can a decision be made on whether to proceed to the next dose group, until the maximum tolerated dose (MTD) is established. It is anticipated that the MTD will be determined within seven dose groups, with a maximum sample size projected to be 42 participants.

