### Dose Group

The starting dose is set at 1.2 mg/m², with dose escalation conducted according to the Modified Fibonacci Scheme, with escalation increments of 100%, 67%, 50%, 40%, 33%, and 33%. The dose escalation increments may be further adjusted based on the pharmacokinetic (PK), pharmacodynamic (PD), and safety data from the previous dose group.

If the maximum dose specified in this protocol (15 mg/m²) has not yet reached the maximum tolerated dose (MTD), the decision to continue dose escalation will be based on PK, PD metrics, and safety data. If PK or PD indicators suggest that the drug has not reached a saturating level of exposure in the body, the dose group will continue to escalate according to the Modified Fibonacci Scheme until MTD is observed or until sufficient drug exposure is achieved (the maximum drug exposure should not exceed the exposure levels observed at the dog HNSTD dose, which corresponds to an equivalent human dose of 36.88 mg/m²). The dose preceding the MTD may be considered the recommended dose for Phase II clinical trials.

Table 7 Dose Escalation Scheme

| **Group Number** | **1** | **2** | **3** | **4** | **5** | **6** | **7** | **…..** |
| --- | --- | --- | --- | --- | --- | --- | --- | --- |
| Escalation Ratio | Starting Dose | 100% | 67% | 50% | 40% | 33% | 33% | 33% |
| Administered Dose (mg/m^2^) | 1.2 | 2.4 | 4.0 | 6.0 | 8.4 | 11.2 | 15 | Previous Dose×33% increment  （Maximum Drug Exposure < 36.88 mg/m^2^） |
| Number of Cases | 3-6 | 3-6 | 3-6 | 3-6 | 3-6 | 3-6 | 3-6 | 3-6 |

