### Escalation Process

The trial begins with a low dose, enrolling 3-6 subjects in each dose group. The decision to proceed to the next dose group will be based on whether at least 3 evaluable subjects from the previous dose group experience Dose Limiting Toxicity (DLT) and the corresponding safety data within 25 days after the first administration. An evaluable subject is defined as one who has received ≥80% of the planned dose or has experienced DLT after at least one dose

The specific regulations for dose escalation are as follows:

Table 8 Dose Escalation Rules

| **Occurrence of DLT** | **Actions** |
| --- | --- |
| No DLT observed | Proceed to the next dose group |
| 1 DLT observed among 3 subjects | Recruit an additional 3 subjects to receive the same dose of the investigational drug and observe for DLT |
| 1 DLT observed among 6 subjects | Proceed to the next dose group |
| ≥2 DLTs observed among 3 or 6 subjects | Reduce to the previous dose group.   - If there are fewer than 6 evaluable subjects in the previous dose group, recruit an additional 3 subjects to reach a total of 6 evaluable subjects. If no more than 1 DLT is observed among the 6 evaluable subjects, terminate the trial, and that dose group will be considered the MTD. - If there are already 6 evaluable subjects in the previous dose group, terminate the trial, and that dose will be considered the MTD. |

**Enrollment Sequence for Subjects in the Same Dose Group:** At the beginning of each dose group, only 1 subject will be enrolled to observe the tolerability and safety of that subject within 25 days after the first administration.

- Only if this subject does not experience DLT can the remaining 2 subjects in the same dose group be enrolled simultaneously.
- If this subject experiences DLT, enrollment of the third subject can only occur after the second subject has completed the 25-day observation period following the first administration, and only if the second subject has not experienced DLT.

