# Trial Population

## Sample Size

This trial is provisionally set to include 7 dosage groups, with a planned enrollment of 21-42 participants primarily consisting of patients with B-cell-related tumors in the category of relapsed or refractory hematologic malignancies.

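### The dose-linearity rule treats failure to reject a slope of 1 as proof of proportionality, so the less precise the data, the easier it is to pass

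*Protocol*

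**What the plan says.** Section 10.5 (Pharmacokinetic Analysis) says the single-dose parameters will be "analyzed with a power function model to examine the relationship between AUC, C_max_, and dose". It then fixes the decision rule: "The linearity criterion will be that the 95% confidence interval for the β value includes 1". It sets no equivalence bounds, no precision requirement and no inconclusive outcome.

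The data feeding this rule are sparse. Section 3.2.4 describes "enrolling 3-6 subjects in each dose group", and section 4.1 states: "This trial is provisionally set to include 7 dosage groups, with a planned enrollment of 21-42 participants". The ladder runs from 1.2 to 15 mg/m² (section 3.2.3, Table 7). Section 3.1 has escalation continue only "until the maximum tolerated dose (MTD) is established", so the upper groups may never open.

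The preclinical evidence on proportionality is mixed. In rats (section 1.4.3.1), "A tenfold increase in dose corresponded to a 21.7-fold and 24.4-fold increase in AUC_0-last", while C0 is described as proportional. In dogs (section 1.4.3.2), AUC and Cmax are described as rising linearly from 0.3 to 3 mg/kg.

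**The concern.** A 95% interval that includes 1 shows that the data are compatible with proportionality. It does not show that they are incompatible with a material departure. Used as a criterion for linearity, it puts the burden of proof the wrong way round: a wider interval passes more readily, and a very precise study can fail on a trivial departure.

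This design makes wide intervals likely. Groups are small, and stopping early at the MTD reduces both the number of subjects and the dose range. At stake is whether a statement of linear PK in the report has been earned by the data.

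**Working it through.** **Inputs**
- Doses 1.2, 2.4, 4.0, 6.0, 8.4, 11.2 and 15 mg/m² (Table 7), so the full range is r = 15/1.2 = 12.5.
- 3 to 6 subjects per group, giving 7×3 = 21 to 7×6 = 42, which matches section 4.1.
- Human between-subject variability is not stated. Assumption: SD of ln(exposure) σ = 0.5, with 0.3 and 0.7 as the range.

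**1. Preclinical slopes.** The rat AUC "values were 55.3 ± 3.68, 248 ± 36.1, and 1280 ± 122 ng.h/mL, respectively" at 1, 3 and 10 mg/kg. The ratio 1280/55.3 = 23.1 lies between the stated 21.7 and 24.4. For a tenfold dose, slope = log10(fold increase): log10(21.7) = 1.34, log10(23.1) = 1.36, log10(24.4) = 1.39. I use 1.36. The dog AUC gives 713/75.1 = 9.49, so log10 = 0.98.

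**2. What a slope means at the top dose.** Departure from proportional exposure = r^(β−1). For β = 1.2: 12.5^0.2 = 1.7 times. For β = 1.36: 12.5^0.36 = 2.5 times.

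**3. Chance that the protocol's rule declares linearity.** In a log-log regression, SE(β) = σ/√Sxx, where Sxx is the sum of squared deviations of ln(dose). The rule passes when |estimate − 1| ≤ t(0.975, N−2) × estimated SE. With δ = (β−1)/SE, the probability is F(t; N−2, δ) − F(−t; N−2, δ), where F is the noncentral t distribution.

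- 7×3: Sxx = 14.33. At σ = 0.5, SE = 0.132 and the 95% half-width is 2.093 × 0.132 = 0.28.
- 7×6: Sxx = 28.67. At σ = 0.5, SE = 0.093 and the half-width is 2.021 × 0.093 = 0.19.

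| Design | True slope | σ = 0.3 | σ = 0.5 | σ = 0.7 |
|---|---|---|---|---|
| 7×3 | 1.0 | 95% | 95% | 95% |
| 7×3 | 1.2 | 33% | 70% | 82% |
| 7×3 | 1.36 | 1% | 27% | 54% |
| 7×6 | 1.2 | 6% | 45% | 68% |
| 7×6 | 1.36 | 0% | 4% | 23% |

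At 7×3 and σ = 0.7, a proportional drug passes in 95% of trials and one with slope 1.2 in 82%, so a pass says little.

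**4. Early stopping.** Under Table 8, two or more DLTs end escalation, and the previous group is brought to 6 evaluable subjects. The smallest samples are then 3+3+3+6+3 = 18 (stop at group 5, r = 8.4/1.2 = 7) and 3+3+6+3 = 15 (stop at group 4, r = 6.0/1.2 = 5). At σ = 0.5, a slope of 1.36 is called linear in about 53% and 70% of trials. If the top group had itself reached 6 before stopping, the figures are 45% and 63%.

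**5. An alternative rule.** Require the 90% CI to lie within 1 ± ln(2)/ln(r). For r = 12.5 this is 1 ± 0.693/2.526, or 0.73 to 1.27. At σ = 0.5, a truly proportional drug meets these bounds in about 29% of 7×3 trials and 79% of 7×6 trials. A slope of 1.36 meets them in about 1% of 7×3 trials.

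**The case against.** The strongest reply is that little depends on this rule. PK is a secondary objective (section 2.2), the analysis is mainly descriptive (section 10.2), and section 10.8 leaves detailed methods to the statistical analysis plan. Much of this stands and limits the weight of the point. It does not remove it, because section 10.5 does not defer the rule but states it.

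A reader might infer that a departure as large as the rat one would usually be missed. The figures do not support that. On the full ladder at σ = 0.5 it is detected in 73% of 7×3 trials (100 − 27) and 96% of 7×6 trials (100 − 4). It is missed more often than not only with early stopping or variability near the top of the assumed range, and the protocol gives no human variability to settle which applies. The rat slope is also only one scenario. Dog AUC had a slope of about 0.98 with flat clearance (68.4, 73.4 and 71.5 mL/min/kg), and the protocol itself describes the rat AUC excess as slight.

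A reader might also infer that a default finding of linearity would support dosing above 15 mg/m² or set the Phase II dose. The protocol makes no such link. Section 3.2.3 bases further escalation on PK, PD and safety data under a separate exposure ceiling, and it ties the Phase II dose to the MTD. A slope above 1 also means exposure rising faster than dose, so overlooking it would not by itself create an argument about saturation.

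Finally, the twofold bounds are a choice, and a truly proportional drug would often fail to meet them. That is a fair criticism of any particular bounds, but not a defence of a rule that has none.

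**Conclusion.** The criterion is wrong as written: it equates non-rejection with proportionality and becomes easier to satisfy as information falls. The effect is clearest for moderate departures. At an assumed σ of 0.5, a slope of 1.2 is labelled linear in 70% of trials at the minimum sample size and 45% at the maximum. For a slope of 1.36 the full-ladder figures are 27% and 4%, rising to about 53% or 70% if escalation stops at group 5 or 4 at the smallest sample Table 8 allows.

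All these percentages rest on the assumed variability; the logical fault does not. The consequence is an unearned statement in the secondary PK results, not a faulty escalation decision. A wording change is warranted.

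**What to change.** Replace the linearity sentence in section 10.5 as follows:
- For AUC and Cmax, report the power-model slope with its 90% CI and the implied exposure ratio for a doubling of dose, 2^β (for example 2^1.36 = 2.6).
- Conclude proportionality only if the CI lies wholly within bounds fixed in advance and tied to the dose range actually studied. One choice is 1 ± ln(2)/ln(r): 0.73 to 1.27 for r = 12.5, and 0.64 to 1.36 if the ladder ends at group 5 (r = 7). The sponsor may justify other bounds.
- If the CI is not within the bounds, report *not proportional* when it excludes 1 and *inconclusive* when it does not.

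The change needs no extra subjects or samples. Its price is that inconclusive results will be common. At σ = 0.5, a truly proportional drug would meet the twofold bounds in only about 29% of 7×3 trials and 79% of 7×6 trials (91% of 7×3 trials at σ = 0.3). That reflects what groups of this size can show. The bounds also widen as the range shortens, so any conclusion should be stated for the studied doses only.

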| **PK blood collection points** | **Single-Dose Phase****:**  **The PK sampling points have been adjusted as follows based on the pharmacokinetic results and tolerability observed in the first patient**：  Blood samples of 3 mL will be collected from the antecubital vein of the forearm at the following time points: within 0.5 h before administration, and at 5 min, 10 min, 20 min, 30 min (immediately after administration), 32 min, 35 min, 45 min, 1 h, 2 h, 4 h, 8 h, and 12 h after administration, using an indwelling needle.  **Multiple-Dose Phase:**  D11：Blood samples were collected in 3 mL within 0.5 h prior to administration；  D15：Blood samples of 3 mL were collected 0.5 h before, 5 min, 10 min, 20 min, 30 min (immediately after the end of administration), 32 min, 35 min, 45 min, 1 h, 2 h, 4 h, 8 h, and 12 h, respectively. |
| **Biomarker blood collection points** | **Single-Dose Phase**：  Blood samples of 4 mL were collected within 0.5 h before, 1 h, 4 h, 24 h, and 48 h after the end of drug administration.；  **Multiple-Dose Phase:**  D8 Blood samples of 4 mL were collected within 0.5 h before, 1 h, 4 h, and 12 h after administration;  D11 Blood samples of 4 mL were collected within 0.5 h before and 1 h after administration;  D15 4 mL of blood samples were collected within 0.5 h before, 1 h, 4 h, 24 h, 48h and 72 h after administration; |

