**Multiple administration phase（2nd week，D15-D25）**

| Time point | D15 | | | | | | | | | | | | | D17 | D18 | | D19 | D25 |
| --- | --- | --- | --- | --- | --- | --- | --- | --- | --- | --- | --- | --- | --- | --- | --- | --- | --- | --- |
|  | pre-medication | post-drug administration | | | | | | | | | | | | | | | |  |
|  | Within 0.5h | 5min | 10min | 20min | 30min | 32min | 35min | 45min | 1h | 2h | 4h | 8h | 12h | 24h | | 48h | 72h |  |
| PK collects blood samples | **√** | **√** | **√** | **√** | **√** | **√** | **√** | **√** | **√** | **√** | **√** | **√** | **√** |  | |  |  |  |
| Biomarker collection of blood samples * | **√** |  |  |  |  |  |  |  | **√** |  | **√** |  |  | **√** | | **√** | **√** |  |

Note: At the same time point, if there are several examination or procedure items, the priority is as follows: PK blood sample collection > biomarker blood sample collection > vital sign checks > other items.

* Biomarker testing is conducted only for patients with leukemia

The pharmacokinetic blood collection time window is specified in section 7.2.2

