## Multiple-Dose Administration Phase（D8-D25）

After the single-dose administration phase is completed, if the subject tolerates the treatment well, they will enter the multiple-dose administration phase.

- IV Infusion Administration on D8, D11, and D15
- PK Blood Sample Collection:

On D11: collect blood samples 0.5 hours before administration.

On D15: collect blood samples within 0.5 hours before administration, and at 5 minutes, 10 minutes, 20 minutes, 30 minutes (immediately after administration), 32 minutes, 35 minutes, 45 minutes, 1 hour, 2 hours, 4 hours, 8 hours, and 12 hours after administration (3 mL each time).

- Biomarker Blood Sample Collection (only for leukemia patients):

On D8: collect blood samples within 0.5 hours before administration, and at 1 hour, 4 hours, and 24 hours (D9) after administration (4 mL each time).

On D11: collect blood samples within 0.5 hours before administration and at 1 hour after administration (4 mL each time).

On D15: collect blood samples within 0.5 hours before administration, and at 1 hour, 4 hours, 24 hours (D16), 48 hours (D17), and 72 hours (D18) after administration (4 mL each time).

- Vital Signs: Including temperature, heart rate, respiratory rate, and blood pressure (systolic and diastolic), to be checked once within 0.5 hours before each administration and again 2 hours after administration on D8, D11, and D15, as well as once on D25.
- Physical Examination: Includes examination of the skin, mucous membranes, lymph nodes, head, neck, chest, abdomen, spine/extremities, and nervous system. This will be conducted once on D11, D15, and D25.
- Laboratory Tests: These will be conducted once on D11, D15, and D25.
- Complete Blood Count (CBC): Red blood cell count, hemoglobin, platelet count, white blood cell count, neutrophil count, lymphocyte count.
- Urinalysis: Urine protein, urine red blood cells, urine white blood cells.
- Blood Biochemistry: Blood creatinine, urea, total bilirubin, alanine transaminase (ALT), aspartate transaminase (AST), alkaline phosphatase, total protein, albumin, electrolytes (K+, Na+, Ca2+, Mg2+, Cl-), total cholesterol, low-density lipoprotein (LDL), high-density lipoprotein (HDL), creatine kinase (CK), creatine kinase isoenzyme (CK-MB), α-hydroxybutyrate dehydrogenase (α-HBDH), lactate dehydrogenase (LDH), fasting blood glucose.
- Coagulation Function: Prothrombin time (PT), activated partial thromboplastin time (APTT), thrombin time (TT), fibrinogen (FIB).

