## Pharmacokinetics

### Pharmacokinetic Parameters

Pharmacokinetic parameters will be calculated using the professional pharmacokinetic software WinNonlin version 8.1 or higher, utilizing the non-compartmental analysis (NCA) method. The pharmacokinetic parameters include:

Single-Dose Administration Phase: T_max_, C_max_, AUC_(0-t)_, AUC_(0-∞)_, Vd, Ke, T_1/2_, MRT, CL

Multiple-Dose Administration Phase: T_max_, C_ss_min_, C_ss_max_, Css_av, t_1/2_, CL, AUC_ss_

When calculating AUC, actual sampling times will be used for time points that fall outside the sampling window.

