### Sample Collection Timing

Single-Dose Pharmacokinetic Study:

The PK sampling points will be adjusted based on the pharmacokinetic trial results and tolerability observed in the first patient as follows:

For each patient, blood samples of 3 mL will be collected from the antecubital vein using an indwelling needle at the following time points: within 0.5 hours before administration, and at 5 minutes, 10 minutes, 20 minutes, 30 minutes (immediately after administration), 32 minutes, 35 minutes, 45 minutes, 1 hour, 2 hours, 4 hours, 8 hours, and 12 hours after administration.

Multiple-Dose Administration Phase

D11: Blood samples of 3 mL will be collected within 0.5 hours before administration;

D15: Blood samples of 3 mL will be collected within 0.5 hours before administration, and at 5 minutes, 10 minutes, 20 minutes, 30 minutes (immediately after administration), 32 minutes, 35 minutes, 45 minutes, 1 hour, 2 hours, 4 hours, 8 hours, and 12 hours after administration.

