### Sample Handling, Testing, and Storage

Anticoagulant: K_2_EDTA

For each blood collection, 4 mL of peripheral blood will be placed in an anticoagulant collection tube. Peripheral blood mononuclear cells (PBMCs) will be isolated using red blood cell lysis buffer or the Ficoll-Paque method. The isolated PBMCs will be lysed and prepared as samples according to the protocol for Western Blot analysis. The acetylation levels of histones H3 and H4 will be detected using the Western Blot method. Samples will be stored in a freezer at -70 ± 10°C.

Quantitative Analysis Method:

In the single-dose administration phase, the acetylation levels of histones will be referenced to the baseline (Baseline) established from the sample collected 0.5 hours before administration on D1. The results of all time point samples will be quantified, and the trends in histone acetylation levels at each time point will be analyzed. In the multiple-dose administration phase, the acetylation levels of histones will be referenced to the baseline (Baseline) established from the sample collected 0.5 hours before administration on D5. The results of all time point samples will be quantified, and the trends in histone acetylation levels at each time point will be analyzed.

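### The AUC accumulation ratio rests on a 0–48 h single-dose window that the 12 h PK schedule does not cover, and the multiple-dose biomarker baseline is a D5 sample that is not scheduled

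*Protocol*

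**What the plan says.** **Accumulation.** Protocol section 10.5 obtains accumulation by "comparing Cmax and AUC_SS_ from multiple dosing with C_max_ and AUC_0-48h_ from single dosing to calculate the accumulation ratio". Section 7.2.2 ends PK sampling, on D1 and again on D15, with "32 minutes, 35 minutes, 45 minutes, 1 hour, 2 hours, 4 hours, 8 hours, and 12 hours after administration". It introduces the single-dose times with "The PK sampling points will be adjusted based on the pharmacokinetic trial results and tolerability observed in the first patient as follows". The synopsis, the sampling flowchart and sections 6.2 and 6.3 give the same 12 h end. The flowchart's 24 h and 48 h columns for D1 are ticked for biomarkers only. Section 7.2.1 lists the parameters as "Single-Dose Administration Phase: T_max_, C_max_, AUC_(0-t)_, AUC_(0-∞)_, Vd, Ke, T_1/2_, MRT, CL", and for the multiple-dose phase lists AUCss without an interval.

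**Biomarker baseline.** Section 7.3.3 uses the D1 pre-dose sample for the single-dose phase. For the multiple-dose phase it uses a baseline "established from the sample collected 0.5 hours before administration on D5". Section 10.7 speaks of a baseline half an hour before administration and names no day.

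**Biomarker times.** The synopsis has "D8 Blood samples of 4 mL were collected within 0.5 h before, 1 h, 4 h, and 12 h after administration"; the flowchart and sections 6.3 and 7.3.2 put the last D8 sample at 24 h. After the D15 dose, section 6.3 has "24 hours (D16), 48 hours (D17), and 72 hours (D18) after administration". The header of the flowchart for that week reads, after D15, "D17 | D18 | | D19 | D25".

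**The concern.** These are stated rules that the trial's own schedule cannot supply, which is different from detail left to a statistical analysis plan.

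An AUC accumulation ratio is interpretable only if numerator and denominator cover the same interval, or if each is extrapolated by a stated rule. Here the denominator runs 36 h past the last sample and the numerator has no stated window. Two analysts could follow the text and report different ratios from the same concentrations.

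The D5 reference leaves the multiple-dose biomarker change without a reference sample. An analyst must pick D8 pre-dose (after one dose) or D1 pre-dose (untreated), and that choice alters every change from baseline in that phase. The conflicting D8 and D15 times affect which tubes are drawn and how they are labelled.

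PK and PD after single and multiple infusions are both secondary purposes of the trial (section 2.2).

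**Working it through.** The plan gives no figure to reproduce. The check compares the schedules and then bounds the possible size.

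1. **PK window.** Last PK sample: 12 h on D1 and D15. Unsampled part of 0–48 h: 48 − 12 = 36 h, or 36/48 = 75% of the window.

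2. **Dosing gaps.** Doses fall on D1, D8, D11 and D15. The gaps are 7, 3 and 4 days (168, 72 and 96 h). None is 48 h and they are not constant, so the schedule does not supply a 48 h interval for AUCss either.

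3. **Share of AUC0–48h inside the sampled 12 h, one-compartment assumption.** No human half-life is given, so the animal plasma half-lives in section 1.4.3 serve as an assumed range: 1.21 h (HCT116 mice), 4.49, 7.05 and 8.47 h (dogs), 12.2 h (Ighmyc mice). For a 0.5 h infusion, with k = ln 2 / t½ and g = (e^(0.5k) − 1)/(0.5k), the share is (1 − g·e^(−12k)) / (1 − g·e^(−48k)). Example at 12.2 h: k = 0.0568, g = 1.014, so (1 − 0.513)/(1 − 0.066) = 0.522.

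| t½ (h) | AUC0–12h / AUC0–48h |
|---|---|
| 1.21 | 0.999 |
| 4.49 | 0.837 |
| 7.05 | 0.691 |
| 8.47 | 0.630 |
| 12.2 | 0.522 |

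   If AUCss were taken over the observed 12 h on D15 and divided by an extrapolated AUC0–48h, a drug with no accumulation would show these values instead of 1. If AUCss were instead taken over 96 h, the same model gives at most 1.066 (at 12.2 h).

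4. **The same share with multi-phasic decline.** The dog data in section 1.4.3.2 allow MRT = Vss/CL:
   - 0.3 mg/kg: 3.69/(68.4 × 0.06) = 0.90 h
   - 1 mg/kg: 3.85/(73.4 × 0.06) = 0.87 h
   - 3 mg/kg: 2.89/(71.5 × 0.06) = 0.67 h

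   One-compartment decline at the dog half-lives would need MRT = t½/ln 2 = 6.48, 10.17 and 12.22 h. The dog curve is therefore strongly multi-phasic. In a bi-exponential curve the slow phase can hold at most f = MRT/(t½/ln 2) of the AUC: 0.139, 0.086 and 0.055. The 12–48 h part of AUC0–48h is then at most f(e^(−12k) − e^(−48k))/(1 − f·e^(−48k)) = 2.2%, 2.6% and 2.0%.

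5. **Biomarker baseline.** Biomarker samples fall on D1, D2 and D3, then from D8 pre-dose onward. Doses on D5: none. Samples on D5: none. A D8 pre-dose sample and a D1 pre-dose sample both exist.

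6. **Biomarker times.** With D15 as the dosing day, 24, 48 and 72 h fall on D16, D17 and D18, as in section 6.3; section 6.2 counts the same way (24 h is D2, 48 h is D3). The flowchart header has no D16 and includes D19. For D8, 12 h stands in one place and 24 h in three.

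**The case against.** Several points on the other side stand.

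- **A reader might infer that the results cannot be computed.** That goes too far. AUC0–∞ is already planned, so terminal-slope extrapolation is already part of the analysis and AUC0–48h could be obtained the same way. It is unobserved, and no rule is stated for it. The Cmax ratio and the single-dose biomarker analysis are unaffected. The first patient may also have been sampled on a longer earlier schedule.
- **A reader might infer a ratio biased to roughly half.** That needs AUCss cut at 12 h, AUC0–48h extrapolated, and one-compartment decline at the longest half-life. The protocol states none of these, and the dog data contradict the last. The Ighmyc mouse data also fit it poorly: the reported plasma MRT is 6.00 h, against 12.2/ln 2 = 17.6 h. If both AUCs are cut at 12 h, or both are extrapolated, most of the distortion goes.
- **A reader might infer that real accumulation could be hidden.** Even at 12.2 h, one-compartment carry-over across the 96 h gap before D15 is 2^(−96/12.2), about 0.4%.
- **A reader might link the ratio to escalation above 15 mg/m².** Section 3.2.3 and the synopsis refer to PK or PD indicators of saturation in general. Neither names the accumulation ratio.
- **A reader might reject D8 as a baseline because it follows a dose.** Section 7.3.3 intends a separate baseline for each phase, and D5 would also have followed the D1 dose. D1 as sole baseline is a preference.
- **The AUCss interval alone** could be left to the analysis plan. It matters here because its comparator is fixed at a window that is not sampled.
- **The flowchart header** is a merged-cell table and may have shifted in extraction. The nominal hours after D15 agree everywhere.

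D5 and 48 h look like remnants of an older schedule: section 6.2 still mentions 3 days of monitoring after D1, where the synopsis and section 3.1 have 6. Table 9 gives windows for 6 h and 10 h, which are not sampled, and none for 12 h. This is an inference.

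**Conclusion.** The point holds in a limited form. Section 10.5 fixes a single-dose AUC window that the current PK schedule does not support, so the AUC accumulation ratio is not properly defined and may compare unequal windows. Its numerical effect is unknown. The bounds run from negligible (short half-life), through about 2–3% (multi-phasic decline as in dogs), to a ratio near 0.52 without accumulation (one-compartment, 12.2 h, windows mismatched). All of these rest on animal data and assumed curve shapes.

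The D5 baseline in section 7.3.3 does not exist in the schedule, and section 10.7 does not resolve which sample replaces it. This concerns leukemia patients only. The 12 h against 24 h conflict on D8 is clear; the D15 day labels are a probable but less certain conflict.

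All of this concerns descriptive secondary PK/PD outputs. DLT assessment and MTD determination do not use them. It should be corrected, but it does not threaten the trial's primary purpose.

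**What to change.** - **Section 10.5:** define the AUC accumulation ratio as AUC0–12h on D15 divided by AUC0–12h on D1, from the identical sampling times, alongside the Cmax ratio. Remove AUC0–48h.
- **Sections 7.3.3 and 10.7:** replace D5 with an existing pre-dose sample and name it in both places. Use D8 if a phase-specific baseline is intended, or D1 if an untreated baseline is intended.
- **Synopsis, flowchart, 6.3 and 7.3.2:** reconcile the last D8 biomarker time and the day labels after D15.

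The cost is protocol wording only. No new samples are needed, because every sample named above is already scheduled.
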